## Abstract

**Background/Objectives**: Necrotizing enterocolitis (NEC) is an inflammatory disease with an incidence of about one in 1000 live births, much higher in premature and low birth weight newborns. Intestinal dysbiosis is an important element in the pathogenesis of NEC, and for this reason, experimental models have been used to administer fecal microbiota transplants (FMTs) for prophylaxis and treatment of NEC with very satisfactory results. The primary endpoint of the study is safety, defined as the incidence of adverse events (AEs) and serious adverse events (SAEs) occurring from the time of intervention until hospital discharge, classified according to severity and assessed for relatedness to the intervention. **Methods**: This prospective, single-arm, open-label clinical study will include 20 infants born between 24 0/7 and 36 6/7 weeks of gestation. FMTs will be administered twice as a deep rectal infusion via a Foley catheter. The donors of the material from which the FMT will be prepared will be women in the third trimester of pregnancy. The safety of the therapy will be assessed by comparison with a control group, i.e., 20 patients who will meet the same inclusion criteria and will not meet any of the exclusion criteria, subject to the same hospital observation but without undergoing any medical/therapeutic intervention other than the collection of biological material. **Discussion**: The study will provide data on the safety and initial efficacy of FMT in this group of patients, which will allow for further research into the use of this method in the prevention of infections and NEC. Ethics: The study protocol was approved by the Bioethics Committee of the Medical University of Warsaw, Warsaw, Poland (KB/52/2025). All procedures will follow the principles of the Declaration of Helsinki. The results of the study will be submitted for knowledge translation in peer-reviewed journals and presented at national and international pediatric society conferences. Clinical Trial Registration: The study is registered at ClinicalTrials.gov: ID: NCT06333405.

## 1. Introduction

Necrotizing enterocolitis (NEC) is an inflammatory disease affecting one in 1000 live-born newborns. Due to NEC, 2–5% of newborns are hospitalized annually in neonatal intensive care and pathology units. Overall, 85% of all cases of NEC occur in neonates born <32 weeks of gestation (WG) and/or weighing <1500 g. The risk increases with decreasing gestational age. At 22–28 WG, it is 11%; at 28–32 WG, it is 9% and increases to 13% with coexisting congenital heart disease [1,2]. The mortality rate in the general population of patients with NEC is between 15 and 30%, depending on the study, and has remained unchanged for many years [3,4]. The current treatment regimen for NEC is based on symptomatic interventions—cessation of enteral feeding, antibiotic therapy, and, in complicated cases, surgical intervention [1].

According to the most recent studies, intestinal dysbiosis, i.e., altered patterns of intestinal colonization, resulting in abnormal intestinal microbiome composition and microbiota function, plays a very important role in the pathogenesis of NEC and other infectious complications, like neonatal sepsis [5,6,7]. Dysbiosis initiates an unbalanced pro-inflammatory response of the immune system in premature infants, which ultimately leads to a breakdown of the intestinal mucosal barrier, intestinal bacterial translocation, and intestinal necrosis [6,8]. In the study by el Manouni el Hassani et al., it was shown that in both Gram-negative and Gram-positive late-onset sepsis LOS combined, the causative pathogen could be identified in at least one fecal sample collected 3 days prior to LOS onset in the majority of the fecal samples, whereas these pathogens were present in about one-third of control samples [9].

Antibiotic therapy in the mother and newborn, method of delivery, birth weight and birth age have been proven to affect the microbiome [6,10]. Vaginal delivery and breastfeeding ensure the formation of the correct microbiota and microbiome pattern of the gastrointestinal tract in the newborn. Breastfeeding is one of the main preventive factors for NEC, but it is often challenging to achieve for premature newborns due to both neonatal and maternal factors. On the other hand, formula feeding predisposes to the development of NEC through significant changes in the intestinal microbiota [11].

At the same time, meta-analyses provide no strong evidence confirming the preventive effect of standardized probiotics against NEC [12]. Studies indicate a potential positive role of probiotics containing Bifidobacterium and Lactobacillus strains, but appear insufficient to restore the natural microbiota, and, in particular, the microbiome, in the face of multifactorial dysbiosis [13,14].

Despite several meta-analyses on the efficacy of probiotics in reducing mortality and morbidity associated with NEC in premature infants, ESPGHAN (European Society for Paediatric Gastroenterology, Hepatology and Nutrition) and AAP (American Academy of Pediatrics) recommendations for administering probiotics to premature infants are cautious. Despite numerous randomized clinical trials, the optimal strain, dose or combination of bacterial strains that could be routinely recommended for supplementation has still not been clearly identified [15,16,17,18].

Since the important role of intestinal dysbiosis in the pathophysiology of NEC has been discovered, it has been hypothesized that the fecal microbiota transplantation (FMT) procedure, which was proven effective in restoring intestinal eubiosis, may have both prophylactic and therapeutic effects in NEC [19,20,21,22]. Moreover, recent data show that FMT can also decolonize antibiotic-resistant bacteria from the gastrointestinal tract of patients and has immunomodulatory or even anti-infective potential [23,24,25].

Recently published reviews of NEC treatment options reiterate FMT as a potentially very promising method for the prevention and treatment of NEC but emphasize the necessity of validating these findings in a clinical trial setting [26,27].

To the best of our knowledge, FMT has not yet been evaluated in a cohort of premature newborns in this specific prophylactic context. For this reason, we have decided to initiate a clinical trial at our center to test the safety and, potentially, the future effectiveness of this method for preventing NEC.

## 2. Experimental Design

### 2.1. Research Hypothesis

We hypothesize that prophylactic fecal microbiota transplantation in preterm infants is safe and well-tolerated, with an adverse event profile comparable to standard care.

### 2.2. Trial Design

This will be a safety study of FMT for the prevention of NEC, in the form of a prospective, open-label study with continuous recruitment of up to 40 patients in total (20 in the study group, 20 in the control group). Included patients must meet the exact inclusion criteria described below and must not meet any exclusion criteria. The study group will include 10 premature infants born between 28 0/7 and 36 6/7 weeks of gestation, followed by another 10 premature infants born between 24 0/7 and 27 6/7 weeks of gestation, and 20 premature infants in the control group. After completion of this stage (inclusion and treatment of 20 patients + 20 in the control group), the safety of the therapy will be assessed with a description and presentation of all adverse events, their classification and relationship to the intervention.

The safety of the therapy will be assessed by comparison with a control group, i.e., 20 patients who will meet the same inclusion criteria and will not meet any of the exclusion criteria, subject to the same hospital observation but without undergoing any medical/therapeutic intervention other than the collection of biological material (including stool, blood and urine samples for exploratory testing of the gut microbiota).

Recruitment will occur continuously between January 2026 and January 2027. The study is registered at ClinicalTrials.gov (NCT06333405).

### 2.3. Participants, Enrollment, Randomization, and Statistical Methods

The studied population will be the group of premature newborns (born between 24 0/7 and 36 6/7) who are at increased risk of developing NEC and who may benefit most from FMT.

#### 2.3.1. Sample Size

A formal sample size calculation based on power analysis was not performed, as this is a pilot safety study intended to generate preliminary data (estimates of adverse event rates) for a future randomized controlled trial (RCT). A sample size of 20 subjects in the intervention group was determined based on feasibility constraints and standard recommendations for pilot safety studies, following biostatistical consultation [28]. In the first phase, 10 patients born between 28 0/7 and 36 6/7 will be included, followed by 10 patients born between 24 0/7 and 27 6/7 in the second phase.

The control group will include 20 matched controls—patients who meet the same inclusion and exclusion criteria as the study patients.

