#### 2.3.2. Allocation

During the safety study phase, we plan to enroll the first 20 patients who meet the inclusion criteria and do not meet the exclusion criteria, who will be admitted to the clinic during the study.

The list will be available to all department physicians who will be involved in the study and trained in study procedures. These will also be the individuals who will decide on the administration of FMT to patients and observe them after the procedure.

Patients will be included in the control and study groups in a 1:1 ratio according to the order of admission to the ward. This means that each subsequent patient included in the study will be included in the opposite group to the previous patient.

The study will not be blinded.

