#### 2.3.3. Statistical Analysis

All analyses will be conducted on an intention-to-treat basis.

The primary endpoint is safety, defined as the incidence of adverse events (AEs) and serious adverse events (SAEs) during the observation period.

The proportion of patients experiencing at least one AE or SAE will be compared between groups using Fisher’s exact test. The chi-square test will be applied when its assumptions are met.

The incidence of specific AEs will also be compared using Fisher’s exact test. Relative risks (RRs) with two-sided 95% confidence intervals (CIs) will be calculated.

If the number of events per patient is analyzed, between-group comparisons will be performed using Poisson regression or negative binomial regression, depending on data dispersion.

Time to first AE, if applicable, will be analyzed using Kaplan–Meier estimates and compared using the log-rank test.

Continuous variables will be assessed for normality using the ShapiroWilk test. Normally distributed variables will be compared using Student’s *t*-test, and non-normally distributed variables using the Mann–Whitney U test.

Two-sided tests will be used throughout, with statistical significance set at α = 0.05. Estimates will be presented with two-sided 95% confidence intervals. Analyses will be performed using validated statistical software (e.g., R, Stata, or SAS); the exact software and version will be documented in the final report.

Given the limited sample size, the study is not powered for formal hypothesis testing of small effect sizes. Therefore, interpretation will focus primarily on effect size estimates and their 95% confidence intervals rather than solely on statistical significance. Clinically meaningful differences will be considered in the context of effect magnitude and precision.

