#### 2.3.4. Inclusion Criteria

Premature babies born naturally or by caesarean section between 24 0/7 and 36 6/7 weeks of pregnancy.At least 24 h after the end of antibiotic therapy, if it is/was used.Up to 6 days of age OR up to 14 days of age in the case of transfer from another facility or temporary contraindications to the administration of microbiota (defined below).Newborns born in the hospital conducting the experiment and outside of it.Premature infants hospitalized in the intensive care unit and neonatal pathology unit during the study period.Signed informed consent of parents/legal guardians for the child’s participation in the experiment in the study group (with the administration of microbiota)—in the version for newborns born between 24 0/7 and 27 6/7 weeks of pregnancy.B. Signed informed consent of parents/legal guardians for the child’s participation in the experiment in the study group (with microbiota administration)—version for newborns born between 28 0/7 and 36 6/7 weeks of gestation.C. Signed informed consent of parents/legal guardians for the child’s participation in the experiment in the control group (without administration of microbiota)—in the version for the control group.

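### The gestational split and phases are set for the FMT group but not for the controls, so alternation conflicts with the phases and the unstratified AE comparison is open to confounding by gestational age

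*Protocol article*

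**What the plan says.** **FMT group.** Section 2.3.1 says "In the first phase, 10 patients born between 28 0/7 and 36 6/7 will be included, followed by 10 patients born between 24 0/7 and" (the sentence goes on to set the upper limit of the second band just below 28 weeks). Section 2.2 gives the same split, and section 4.1 makes the second phase conditional on there being no SAE in the first. The FMT group is therefore half under 28 weeks by design.

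**Controls.** Section 2.2 follows the FMT split with "and 20 premature infants in the control group", undivided. Section 2.3.1 says "The control group will include 20 matched controls—patients who meet the same inclusion and exclusion criteria as the study patients". The gestational criterion in section 2.3.4 is "Premature babies born naturally or by caesarean section between 24 0/7 and 36 6/7 weeks of pregnancy". That section has a separate FMT consent version for each gestational band, but a single one for infants "in the control group (without administration of microbiota)—in the version for the control group". The matching time point in sections 2.3.6, 4.4 and 4.5 concerns the timing of observation, not gestation.

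**Allocation.** Section 2.3.2 says "we plan to enroll the first 20 patients who meet the inclusion criteria and do not meet the exclusion criteria", and then "Patients will be included in the control and study groups in a 1:1 ratio according to the order of admission to the ward", each infant going to the group opposite to the previous one. No strata are mentioned.

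**Analysis.** Section 2.3.3 says "The proportion of patients experiencing at least one AE or SAE will be compared between groups" by Fisher's exact or chi-square test. It adds relative risks, the log-rank test, and the t-test or Mann–Whitney test. Poisson or negative binomial regression is named for event counts, with no covariate. Gestational stratum appears nowhere in that section.

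**The concern.** The introduction states that NEC risk rises as gestation shortens. It is reasonable to expect the same of AEs generally, of antibiotic days and of length of stay. If one arm has a fixed gestational mix and the other takes whatever mix admissions supply, a crude comparison can attribute a difference in prematurity to FMT. Too few controls under 28 weeks would make FMT look harmful. Too many would make it look safer and could hide a real signal.

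This bears on the primary endpoint. Section 2.3.3 says that interpretation will rest mainly on effect estimates and their intervals, and it is the estimate that such an imbalance moves.

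**Working it through.** **1. Can the rules be followed together?** Take a 26-week infant admitted in phase 1 who meets all criteria. If the next place is control, nothing stated bars the infant from it. If the next place is FMT, alternation assigns FMT but the phase does not admit the infant to it. The reverse occurs in phase 2: a 30-week infant may take a control place but not an FMT place. So, on the literal text, the control mix is uncontrolled in both phases and the alternation rule cannot always be carried out. If the phases bind all enrolment, alternation works and gives about 10 controls per stratum. The text does not say which is meant.

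**2. What does an unequal mix do when FMT has no effect?** The only planned figures to reproduce are the sums 10 + 10 = 20 and 20 + 20 = 40, which agree. No power calculation is given.

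Let *k* be the number of the 20 controls under 28 weeks, *h* the risk under 28 weeks and *l* the risk at 28 weeks or more.

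- FMT expected risk = (10*h* + 10*l*)/20
- Control expected risk = (*kh* + (20 − *k*)*l*)/20
- Difference = (10 − *k*)(*h* − *l*)/20

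Inputs: the NEC rates of 11% (22–28 weeks) and 9% (28–32 weeks) come from the introduction. The document gives no AE risk by stratum, so 60%/20% and 80%/30% are assumptions.

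| *h* / *l* | FMT | Controls, *k* = 3 | Controls, *k* = 5 | Controls, *k* = 15 | Difference in points (*k* = 3, 5, 15) |
|---|---|---|---|---|---|
| 11% / 9% (NEC, document) | 10.0% | 9.3% | 9.5% | 10.5% | +0.7, +0.5, −0.5 |
| 60% / 20% (assumed) | 40% | 26% | 30% | 50% | +14, +10, −10 |
| 80% / 30% (assumed) | 55% | 37.5% | 42.5% | 67.5% | +17.5, +12.5, −12.5 |

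On the protocol's RR scale, with *k* = 3, 5 and 15, the null RR is 0.40/0.26 = 1.54, 0.40/0.30 = 1.33 and 0.40/0.50 = 0.80 at 60%/20%. At 11%/9% it is 1.08, 1.05 and 0.95. With *k* = 10 the difference is 0 and the RR is 1.00 for any pair of risks.

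The NEC bands do not coincide with the trial strata and give no rate for 32–36 weeks, so the first row does not show that the bias is small for AEs in general.

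**3. How likely is an unequal mix?** Suppose controls were consecutive admissions regardless of phase, and a share *s* of them were under 28 weeks (both assumed). The binomial chance that 8 to 12 of 20 controls are under 28 weeks is about 0% at *s* = 0.1, 3% at 0.2, 23% at 0.3 and 74% at 0.5.

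**4. Effect on the test.** Exact calculation at assumed risks of 80%/40% with no FMT effect gives a two-sided Fisher rejection rate of 1.3% at *k* = 10, 4.6% at *k* = 4 and 13.1% at *k* = 0. At *k* = 4 the null RR is 0.60/0.48 = 1.25 while the test still holds its 5% level. Moderate imbalance thus shows in the estimate before it shows in the test's error rate.

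**5. Precision when both arms are 10/10.** The standard error of the risk difference at 60%/20% is √(2 × 0.4 × 0.6/20) = 0.155 unstratified, and √(2 × 0.20/20) = 0.141 stratified, where 0.20 is the mean of 0.24 and 0.16. That is about 9% lower. At 11%/9% the ratio is √(0.0899/0.0900) = 0.9994, a negligible gain.

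**The case against.** **The phases may bind everyone.** Section 4.1 speaks of including the 24–27 week infants in the study only in phase two, the controls are called matched, and strict alternation is workable only if enrolment as a whole is phased. On that reading about 10 controls fall in each stratum and no bias is expected. This stands as far as it goes. A reader might infer that the comparison *is* confounded; the documents show only that it is open to confounding.

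**The stopped-phase case.** A reader might infer that, if phase 2 never opens, 10 FMT infants of 28–36 weeks would face up to 20 controls of mixed gestation. The documents do not support this. Under 1:1 alternation about 10 controls would have been enrolled by then, and no passage provides for recruiting controls alone afterwards. What remains is that the gestation of those roughly 10 controls is unspecified.

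**The large figures are assumed.** This is correct. The double-digit shifts come from chosen gaps of 40 to 50 points between strata. In addition, *k* = 15 would need at least 5 controls under 28 weeks in phase 1 even if all 10 phase-2 controls were under 28 weeks.

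**Adjustment may be in the SAP, and the limits are disclosed.** Stratified tests are often left to a SAP, which is not shown, and an unadjusted analysis of balanced arms is valid. Section 5.4 concedes selection bias and residual confounding in general terms and urges caution. This lessens the analysis half of the point. It does not settle the design half: gestational age is known at enrolment and can be balanced, and no later adjustment can supply controls missing from a stratum.

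**Conclusion.** The point holds as a defect of design wording that reaches the primary comparison. The FMT group has a fixed gestational mix, the controls do not, and the alternation rule cannot be reconciled with the phases as written. The unstratified AE comparison is therefore open to confounding by gestational age, in either direction.

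The size cannot be fixed from the document. At 3, 5 or 15 controls under 28 weeks it is under 1 point with the document's own NEC rates, and +14 to −10 points if AE risks were 60%/20%. It is zero if controls are in fact enrolled 10 and 10. The loss of precision from ignoring the stratum is secondary: about 9% in the standard error at 60%/20% and negligible at 11%/9%.

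**What to change.** **Sections 2.2, 2.3.1 and 2.3.2.** State that FMT and control infants are enrolled concurrently within each phase from the same gestational stratum, 10+10 at 28–36 weeks and then 10+10 at 24–27 weeks, with alternation run separately in each stratum. Define *matched* accordingly. State that, if phase 2 does not open, the comparison uses only the phase-1 controls of 28–36 weeks.

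**Section 2.3.3.** Report AEs by stratum and use stratum-adjusted estimates, for example a Mantel–Haenszel RR, an exact stratified test, a stratified log-rank test, and a stratum term in the count regressions.

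**Cost.** Protocol wording and a few lines of code, with no extra infants. The downside is that controls can be enrolled only while their stratum is open.

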#### 2.3.2. Allocation

During the safety study phase, we plan to enroll the first 20 patients who meet the inclusion criteria and do not meet the exclusion criteria, who will be admitted to the clinic during the study.

The list will be available to all department physicians who will be involved in the study and trained in study procedures. These will also be the individuals who will decide on the administration of FMT to patients and observe them after the procedure.

Patients will be included in the control and study groups in a 1:1 ratio according to the order of admission to the ward. This means that each subsequent patient included in the study will be included in the opposite group to the previous patient.

The study will not be blinded.

#### 2.3.3. Statistical Analysis

All analyses will be conducted on an intention-to-treat basis.

The primary endpoint is safety, defined as the incidence of adverse events (AEs) and serious adverse events (SAEs) during the observation period.

The proportion of patients experiencing at least one AE or SAE will be compared between groups using Fisher’s exact test. The chi-square test will be applied when its assumptions are met.

The incidence of specific AEs will also be compared using Fisher’s exact test. Relative risks (RRs) with two-sided 95% confidence intervals (CIs) will be calculated.

If the number of events per patient is analyzed, between-group comparisons will be performed using Poisson regression or negative binomial regression, depending on data dispersion.

Time to first AE, if applicable, will be analyzed using Kaplan–Meier estimates and compared using the log-rank test.

Continuous variables will be assessed for normality using the ShapiroWilk test. Normally distributed variables will be compared using Student’s *t*-test, and non-normally distributed variables using the Mann–Whitney U test.

Two-sided tests will be used throughout, with statistical significance set at α = 0.05. Estimates will be presented with two-sided 95% confidence intervals. Analyses will be performed using validated statistical software (e.g., R, Stata, or SAS); the exact software and version will be documented in the final report.

Given the limited sample size, the study is not powered for formal hypothesis testing of small effect sizes. Therefore, interpretation will focus primarily on effect size estimates and their 95% confidence intervals rather than solely on statistical significance. Clinically meaningful differences will be considered in the context of effect magnitude and precision.

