### 4.4. Procedures for the Patients in the Control Group

Check whether the patient meets the inclusion criteria for the experiment.Check whether the patient meets the exclusion criteria.Discuss the purpose and procedures of the experiment with the patient’s parents/guardians and obtain their informed consent for the child’s participation in the experiment. This includes consent for the processing of personal data and the use of biological material samples for scientific purposes, as well as consent for participation in surveys and follow-up on the effectiveness of therapy.Collect blood parameters indicating inflammation (leukocytosis, CRP, procalcitonin) at the “0” point (“BEFORE intervention”), between signing the consent form and the fifth day of the child’s life.Ensure that biological material samples (feces, urine and blood samples) are collected before (point “0”) FMT, as described in the section below, or collect samples before the sixth day of the child’s life.For the control group, the matching time point for administering gut microbiota doses and counting “post” days is assumed to be the sixth day of the child’s life.From day 6 (the matching time point), any adverse events or deviations from the norm will be recorded, such as deterioration in general condition, appearance of symptoms of infection or increase in inflammation indicators.Blood inflammation parameters (leukocytosis, C-reactive protein (CRP), procalcitonin) will be collected during the “post-matching time point” period at least once within 72 h of day 6, or more frequently if the patient’s clinical condition requires it, as assessed by the attending physician.

The following will also be recorded in both study groups:-The number of days spent in hospital;-Percentage increase in body weight (birth weight vs. weight at discharge);-The number of days of antibiotic therapy received during hospitalization (monitoring until discharge from the hospital conducting the experiment).

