### 5.3. Feasibility and Missing Data Management

Most biological samples will be collected during routine hospitalization, which in this population typically extends for several weeks. Therefore, the majority of scheduled collections will overlap with standard clinical monitoring.

Based on institutional experience, we anticipate an attrition rate of approximately 15%. For safety endpoints, no imputation of missing data will be performed. Analyses will be based on available data. The extent and reasons for missing data will be reported descriptively. Sensitivity analyses may be conducted if the proportion of missing data exceeds 10%.

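### The primary safety endpoint is analysed only as allocated, although infants allocated to FMT can go undosed and then have no start point for counting adverse events

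*Protocol article*

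**What the plan says.** All references are to the protocol article.

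- **Analysis set.** Section 2.3.3: "All analyses will be conducted on an intention-to-treat basis". No exposed or as-treated set is named.
- **Endpoint and comparison.** Section 2.3.3: "The primary endpoint is safety, defined as the incidence of adverse events (AEs) and serious adverse events (SAEs) during the observation period". The main comparison follows: "The proportion of patients experiencing at least one AE or SAE will be compared between groups using Fisher’s exact test".
- **When counting starts.** The Abstract counts events "occurring from the time of intervention until hospital discharge". For controls, section 4.4 says "From day 6 (the matching time point), any adverse events or deviations from the norm will be recorded".
- **How an allocated infant can go undosed.** Ward physicians decide on giving FMT (section 2.3.2). Feeding intolerance, suspected NEC, antibiotics or signs of infection postpone it (section 2.3.6), and postponement ends at day 14 of life (sections 2.3.6 and 4.1). The second dose is also conditional (section 4.3).
- **Missing data.** Section 5.3 does not impute safety data: "Analyses will be based on available data". It adds "we anticipate an attrition rate of approximately 15" per cent, and then "Sensitivity analyses may be conducted if the proportion of missing data exceeds 10" per cent.

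**The concern.** Section 2.1 hypothesises an adverse event profile similar to that of standard care, and section 2.3.1 says the pilot is meant to supply event-rate estimates for a later randomised trial. Both need the event rate in infants who received FMT. An as-allocated analysis puts undosed infants in the FMT denominator, while the Abstract's window gives them no day from which an event could count.

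If those infants behave like controls, or can record nothing, a real harm shrinks towards the hypothesised similarity, and a zero-event result looks more reassuring than the exposure supports. If they are sicker and their events are counted, FMT is charged with events it did not cause. In both cases the estimate answers a question other than the safety of FMT.

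The missing-data rule adds a second uncertainty. It does not say how an infant with incomplete follow-up enters an intention-to-treat denominator, and it leaves the sensitivity analysis optional at a level of missingness that the plan already expects.

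**Working it through.** **Inputs from the protocol.** 20 infants per group (section 2.2); attrition about 15%, trigger 10% (section 5.3). The protocol states no event rate, effect size, power or non-dosing rate, so there is no figure of its own to reproduce.

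**Assumptions.** Event risk 20% in controls and 40% in dosed infants; *k* of 20 FMT infants undosed, with *k* from 1 to 5; risk in the undosed *u* equal to 20% (as controls), 0% (nothing recordable) or 80% (sicker, events counted).

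**Step 1: effect in dosed infants.** Risk difference (RD) = 0.40 − 0.20 = 0.20; RR = 0.40/0.20 = 2.00.

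**Step 2: as-allocated effect.** FMT-arm risk = [(20 − k) × 0.40 + k × u]/20, compared with 0.20.

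| k | u | FMT-arm risk | RD | RR |
|---|---|---|---|---|
| 1 | 20% | (7.6 + 0.2)/20 = 0.39 | 0.19 | 1.95 |
| 3 | 20% | (6.8 + 0.6)/20 = 0.37 | 0.17 | 1.85 |
| 5 | 20% | (6.0 + 1.0)/20 = 0.35 | 0.15 | 1.75 |
| 3 | 0% | 6.8/20 = 0.34 | 0.14 | 1.70 |
| 3 | 80% | (6.8 + 2.4)/20 = 0.46 | 0.26 | 2.30 |

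The shift is zero when *u* equals the dosed risk of 40%, downward below that and upward above it. So the sign depends on who is left undosed.

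**Step 3: zero events.** The two-sided 95% Clopper–Pearson upper limit for 0 of *n* is 1 − 0.025^(1/n). For 0/20 it is 16.8%; for 0/17 (three undosed) it is 19.5%. The as-allocated denominator understates the limit by 2.7 percentage points.

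**Step 4: incomplete follow-up.** 15% of 20 is 3 infants per group. Take an illustrative 6/17 against 3/17 observed.

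- Available-case RD = 6/17 − 3/17 = 0.18.
- Best case for FMT (missing FMT infants event-free, missing controls with events): 6/20 − 6/20 = 0.00.
- Worst case for FMT (the reverse): 9/20 − 3/20 = 0.30.

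Attrition at the planned level can therefore move this RD anywhere between no difference and 30 percentage points.

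**The case against.** **Dilution is not certain.** A reader might infer that undosed infants always hide harm. The documents do not support this. Infants still undosed at day 14 are those with persisting contraindications, such as suspected NEC or signs of infection, and are plausibly sicker. The 80% row shows the opposite error. This objection stands and makes the direction conditional, but it does not make the as-allocated estimate describe exposed infants.

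**The 15% is not a non-dosing rate.** A reader might take 3 of 20 undosed from section 5.3. That section gives 15% as attrition, directly after text on collecting biological samples, and sampling runs to day 120 whereas the Abstract's event window ends at discharge. This stands: *k* is an assumption throughout.

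**Available data and intention to treat.** A reader might call these contradictory. Intention to treat fixes the group in which an infant is analysed, and using the outcomes available within that group is common practice. The two rules are unreconciled, not contradictory.

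**The plan may aim at 20 treated infants.** Section 2.2 describes the stage as complete once 20 patients have been included and treated. If undosed infants are to be replaced, 0/20 could be a count of exposed infants. But section 2.2 also caps recruitment at 40, the article states no replacement rule, and under intention to treat an undosed infant would still belong to the FMT group.

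**The consequence is limited.** Section 2.3.3 puts estimates and intervals ahead of tests, section 5.4 warns against reading non-significance as absence of effect, and section 4.3 gives dosed infants their own 72-hour monitoring, so events soon after exposure will be identifiable. All true. But the emphasis on estimates makes it more important that the estimate refers to exposed infants. Nor is this a detail left to an unseen analysis plan: the article itself commits every analysis to intention to treat.

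**Conclusion.** The point holds in a limited form. The primary safety analysis has only an as-allocated set, the protocol's own rules allow undosed infants in the FMT group, and the event window has no start for them. If any infant goes undosed, the FMT event rate, its upper limit and the RR will not describe exposed infants.

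The size is modest. Under the assumed 40% against 20%, RR 2.00 becomes 1.95 to 1.75 for 1 to 5 undosed at control-level risk, 1.70 for 3 undosed with nothing recordable, and 2.30 for 3 undosed at 80% risk. A zero-event upper limit of 16.8% would stand where 17 exposed infants support 19.5%. All of this rests on assumed event rates and numbers undosed.

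Separately, the expected attrition already exceeds the plan's own trigger for a sensitivity analysis that remains optional. This should be corrected before analysis; it does not invalidate the design.

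**What to change.** 1. In section 2.3.3, define the primary safety set as infants who received at least one FMT dose (the first dose alone counts), compared with controls followed from the matching time point.
2. Before that, reconcile the matching time point: section 4.4 sets it at day 6 of life for controls, while section 2.3.6 lets it be postponed for controls as dosing is for the study group. The comparison cannot be fixed until these agree.
3. Keep the as-allocated analysis as supportive. List undosed infants with reasons, and start their event counting on the same matching day as is used for controls.
4. In section 5.3, state how infants with incomplete follow-up enter the denominator. Replace the optional sensitivity analysis with a planned one that reports both bounds: missing FMT infants event-free with missing controls having events, and the reverse. Showing only the worst case would move the result by assumption alone.

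**Cost.** Mainly analysis wording, plus settling the matching time point. Denominators become slightly smaller and intervals wider, and the exposed-set comparison is no longer strictly as allocated, which is why the as-allocated analysis should be reported beside it.
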